## Abstract

**Background:**

Transient ischaemic attack (TIA) and migraine can generate identical symptoms but have very different short-term risks of stroke. Uncertainty about the diagnosis may lead to missed opportunities to prevent stroke if TIA is treated as migraine, or overtreatment if migraine is treated as TIA. This project aims to define the risk of stroke for people with migrainous symptoms reviewed as suspected TIA and develop a risk assessment tool that could promote standardisation of care.

**Methods and analysis:**

The project involves two interlinked studies:

(1) Study A: prospective observational cohort study.

Setting: NHS TIA and stroke services.

Population: adults with migrainous symptoms undergoing review for suspected TIA by a TIA/stroke service and the initial specialist clinician symptom-based diagnosis is either possible migraine or possible TIA with migrainous symptoms.

Data collection: baseline clinical characteristics, investigations and treatments. Stroke, TIA and migraine events within 90 days.

Sample size: 2709 participants.

Main analyses: analysis of stroke risk, development of stroke risk prediction model, preparation of visual tools to represent the risk model.

(2) Study B: qualitative co-design study.

Setting and population: clinicians from NHS TIA and stroke services.

Data collection: focus groups/interviews exploring views about the potential role for a risk assessment tool, the most appropriate visualisation for the risk tool and barriers/facilitators for implementation.

Sample size: approximately 16 clinicians.

Analyses: framework approach using the Implementation Research Logic Model.

**Ethics and dissemination:**

This study has ethical, Health Research Authority and participating NHS Trust approvals. Dissemination of study results will include presentations at national and international conferences and events, publication in peer-reviewed journals, and plain English summaries for patient/public engagement activities.

**Trial registration number:**

ISRCTN16775533.

STRENGTHS AND LIMITATIONS OF THIS STUDYStudy A in this project is a large observational cohort study sufficiently powered to determine the risk of stroke for people with migrainous symptoms reviewed as suspected TIA.The inclusion of study B, a qualitative co-design process to inform the visualisation of a risk assessment tool and barriers/facilitators to implementation, will support future adoption into clinical services.A limitation of this project is that external validation of the risk prediction model is not planned due to available resources; only internal validation will be undertaken.

## Background

 Stroke affects 110 000 UK citizens each year at a health and social care cost exceeding £9 billion.^1 2^ National healthcare policy aims to reduce stroke-related disability and its wider impact through targeted primary and secondary prevention.^3^ Before a stroke, many patients experience a Transient Ischaemic Attack (TIA), which is a brief episode of neurological impairment due to a temporary reduction in cerebral blood flow. TIA is associated with a 5% risk of stroke after 7 days and 10% during the next 90 days.^4 5^

Although medical treatments cannot completely eradicate stroke risk, meaningful reductions can be achieved.^6 7^ For example, antiplatelet medication produces an absolute risk decrease between 1.1% to 3.6% according to the agent(s) and population.^8^ Therefore, it is important to promptly and accurately identify TIA so that personalised prevention can be initiated and patients given relevant information, such as temporary restrictions on driving. In the NHS, there is a target for patients with suspected TIA to be reviewed by a specialist hospital service within 24 hours of symptoms being reported to initiate appropriate early treatment including antiplatelet, lipid lowering and/or blood pressure control medication, anticoagulation for atrial fibrillation, and surgical endarterectomy if carotid stenosis is present.^6 9 10^

The incidence of first-ever TIA is approximately 50 per 100 000 people per year;^4 5^ however, there are approximately twice this number of referrals to TIA services because of diagnostic uncertainty.^11^ While many TIAs produce classic movement, sensory, speech and visual impairments lasting <20 minutes on a background of vascular risk factors such as hypertension and diabetes, other conditions can cause transient neurological symptoms. Typically half of the referrals made to TIA services are given a different possible or definite diagnosis following specialist review.^11^

Migraine is the single the most common alternative diagnosis among referrals to TIA services. Migraine affects 20% adults of all ages^12^ and is proposed as an explanation for one in eight people referred with suspected TIA.^13^ However, differentiating between migraine and TIA is challenging because of the brief and often subjective nature of symptoms.^13^ Most episodes are not witnessed by a clinician, and by definition, there are no residual physical examination findings. Migraine typically involves a combination of headache, spreading ‘positive aura’ symptoms (eg, visual phenomena including teichopsia, tingling), nausea, increased sensitivity to light and/or sound, and often with a previous history of similar episodes with common triggers (eg, sleep deprivation, hunger, prolonged visual stimulation).^12^ But it is known from longitudinal studies that individuals who regularly experience aura (approximately one third of all migraine sufferers) can also develop ‘negative’ symptoms which are identical to TIA, such as language impairment and limb weakness.^12 14^ During the ‘acephalgic’ variant of migraine, there is little or no headache, whereas headache is reported by up to one third of patients during TIA.^12 15^ Amongst migraine sufferers it has also been shown that genuine TIA can trigger migrainous symptoms,^16^ thereby further increasing diagnostic uncertainty.

Investigations have a limited role in differentiating true migraine from TIA with migrainous symptoms as only 17% of patients with confirmed classic TIA show confirmatory changes of recent cerebral blood flow disturbances on brain imaging,^17^ and following TIA with ‘non-classic’ symptoms estimates vary between 9% and 23%.^17 18^ There is no diagnostic test for migraine. Whilst two diagnostic algorithms for TIA have been developed (the Dawson TIA score^19^ and the Diagnosis of TIA (DOT) score),^20^ neither focuses specifically on migrainous presentations, and neither is used in clinical practice due to concerns about their relevance and accuracy having been developed in single service settings.

Currently, therefore, when patients with migrainous symptoms are being reviewed as suspected TIA, individual clinician judgement based on symptom description and previous medical history is frequently used to determine the diagnosis and management. When there is uncertainty about an important diagnosis, a risk-profile approach may be appropriate to guide treatment, but there is currently no risk-score or algorithm to standardise the interpretation of clinical information for suspected TIA patients with migrainous symptoms. Because migraine is common and can present at any age, it often co-exists with other health problems such as hypertension and diabetes, and therefore a simple demographic stratification approach may lead to both large scale under and over treatment depending on whether the individual clinician places more emphasis on the patient’s symptoms or their vascular risk profile.

Further inconsistency in TIA diagnosis and treatment recommendations may also arise because services are provided by hospital specialists with different backgrounds (eg, neurology, geriatric medicine and acute medicine) whereby speciality-dependent training results in differences in exposure to non-TIA conditions. For example, neurologist training and practice includes diagnosis and management of chronic headache, but this is not the case for geriatric or acute medicine. In addition, TIA services are often supported by nurse specialists and trainee doctors, which may further increase variations in diagnosis and treatment. Service pathways also vary, with some involving initial telephone triage before a standard in-person appointment, whilst full remote assessment by phone and video has been accelerated by the COVID-19 response.^21^

This research will address some of the uncertainty for both clinicians and patients faced with migrainous symptoms reviewed as suspected TIA. As it is currently unclear what information is used in diagnostic decision-making, what treatments are offered, and how stroke risk differs according to the specialist diagnosis assigned, data will be collected to describe current practice and report current stroke risk. The information obtained will then be used to characterise high and low stroke risk groups irrespective of the diagnosis assigned and develop a standardised stroke risk assessment. A standardised stroke risk assessment could be used to guide treatment more effectively than clinical judgement alone.

## Methods and analysis

### Study objectives

To describe baseline clinical characteristics, investigations and treatments for people with migrainous symptoms reviewed as suspected TIA, including description according to the specialist clinician view of whether the diagnosis was more likely migraine or TIA with migrainous symptoms.To describe the proportion of people with migrainous symptoms reviewed as suspected TIA who experience at least one clinically documented hospital admission for stroke during the next 90 days and to compare proportions according to the specialist clinician view of whether the diagnosis was more likely migraine or TIA with migrainous symptoms.To report how key features of TIA services influence: the specialist clinician view of more likely diagnosis of migraine or TIA with migrainous symptoms, specific investigations undertaken, treatment recommendations provided, patient outcomes at 90 days.To describe important characteristics of stroke events occurring within 90 days for people with migrainous symptoms reviewed as suspected TIA, including description according to the specialist clinician view of whether the diagnosis was more likely migraine or TIA with migrainous symptoms.To describe important treatment-related side effects occurring within 90 days for people with migrainous symptoms reviewed as suspected TIA, including description according to the specialist clinician view of whether the diagnosis was more likely migraine or TIA with migrainous symptoms.To create a statistical model using clinical characteristics to predict the risk of stroke for people with migrainous symptoms reviewed as suspected TIA irrespective of the specialist clinician view of the more likely diagnosis, and propose at least one matching risk assessment tool.To obtain and incorporate clinician views about the content, format and future implementation strategy of a risk assessment tool.

### Research design

Two parallel studies are being conducted which will interact to synergistically address the study objectives.

Study A: prospective observational cohort study (addresses objectives 1–6).

Study B: qualitative co-design study (addresses objective 7).

### Study A: prospective observational cohort study

#### Setting

The study is taking place within UK NHS hospital TIA and stroke services, selected to reflect a nationally representative range of regions, referral volumes and host specialties (eg, stroke, neurology, care of the elderly, clinical pharmacology).

#### Population

Inclusion criteria:

Adults with migrainous symptoms reviewed as suspected TIA by a TIA/stroke service.Initial review conducted within 1 week of last symptoms.Following initial review, a specialist clinician symptom-based diagnosis is either possible migraine or possible TIA with migrainous symptoms.At least 40 years old.Able to provide informed research consent.

Exclusion criteria:

Suspected/confirmed TIA without any migrainous features.Clear alternative diagnoses after initial review e.g. seizures.Previous stroke.Referral already made or planned for surgical intervention to prevent stroke e.g. carotid endarterectomy or atrial septal defect closure.Currently under secondary care review for the same neurological symptoms.Cognitive difficulties preventing consent and/or description of subjective symptoms.Life expectancy <90 days.Day 90 follow-up is not possible e.g. resident outside of the service boundary.

#### Participant identification and consent

Potential participants are identified by NHS clinicians involved in conducting urgent TIA assessments which cover all of the eligibility criteria listed above. Commonly, TIA services operate as a one-stop hospital-based review, either via attendance at an outpatient clinic appointment or sometimes via an urgent assessment performed by TIA clinicians in the emergency department. Occasionally, TIA reviews are undertaken by telephone/video conferencing and investigations are performed separately.

Once a potential participant is identified as study eligible, a choice of different approach and consent methods are available to the NHS team according to circumstances:

If a potential participant can be approached in person whilst attending a hospital appointment, a research trained member of staff will introduce the study, provide an information sheet and subsequently obtain consent in writing (online supplemental file 1). If a potential participant requires additional time after the appointment to consider study involvement, a study postal consent form and reply-paid envelope will be issued. Telephone follow-up can be undertaken if the postal consent form is not returned, including the option to take consent verbally.

If a potential participant is only undergoing telephone/video-conferencing appointments with the TIA team, the study will be introduced during the consultation and an invitation letter, the information sheet and a postal consent form/reply paid envelope subsequently mailed or emailed according to preference. Telephone follow-up can be undertaken if the postal consent form is not returned, including the option to take consent verbally.

There may also be situations where a rapid review (in person or telephone/video) either prevents the study being introduced or provides very limited time for discussion. In such instances, an invitation letter, the information sheet and a postal consent form/reply paid envelope will subsequently be mailed or emailed. Similar to above, if the postal consent form is not returned, telephone follow-up can be undertaken.

#### Data collection

Study data are collected by NHS staff and entered into an industry standard secure online database managed by the study co-ordinating centre team based at Newcastle University, UK. All data are labelled with a unique study ID number only.

##### Baseline data collection

This study requires a comprehensive description of patient symptoms and to facilitate recall, baseline data collection is performed within 1 week of the TIA review. The data may be collected directly from the patient during the TIA review, from the medical notes made by the clinician at the review, and/or via an additional telephone/video-conferencing/in person discussion held with the participant at the earliest opportunity (and within 1 week of the review).

The information being obtained at baseline is summarised in table 1.

**Table 1 T1:** Data collected at baseline

Clinical setting and assessor	Date of TIA clinical review Setting of TIA clinical review Role and background of specialist clinician who performed the main assessment Specialist clinician view of more likely diagnosis (migraine/TIA with migrainous symptoms) Specialist confidence rating of diagnosis chosen (very high/high/uncertain)
Patient demography	Age Sex Gender Ethnicity Highest educational level
Patient symptoms	Date/time of first onset of symptoms for the study qualifying (referring) event If more than one discrete episode of symptoms has occurred since the study qualifying (referring) event, number of episodes and date/time of last episod For the study qualifying (referring) event and last episode of symptoms before the TIA clinical review, the presence/absence of the following are recorded: Headache including locations affected and pain rating Nausea or vomiting Dizziness, vertigo or pre-syncope Sensitivity to light Sensitivity to noise Vision symptoms, eye affected and type (wavy lines/zig zag lines/flashes/kaleidoscope changes/large blobs/blurry or pixelated vision/seeing items which appeared to be shimmering/seeing items as smaller than normal (micropsia)/seeing items as larger than normal (macropsia)/seeing an image after it has gone (palinopsia)/seeing straight lines as wavy lines (metamorphopsia)/complete loss of vision (blackness)/other) Difficulty using arm(s) including side and severity (weaker or less coordinated than usual/complete weakness) Difficulty using hand(s) including side and severity (weaker or less coordinated than usual/complete weakness) Difficulty using leg(s) including side and severity (weaker or less coordinated than usual/complete weakness) Facial droop (drooping mouth/drooping eyelid) Tingling/pins and needles in face including side Tingling/pins and needles in whole arm(s) including side Tingling/pins and needles in hand(s) including side Tingling/pins and needles in leg(s) including side Numbness/loss of sensation in face including side Numbness/loss of sensation in arm(s) including side Numbness/loss of sensation in leg(s) including side Difficulty talking and type (slurred words/wrong words/no words) Difficulty hearing and type (lost or muffled hearing/ringing or tinnitus/sensitivity to noise) Concentration or memory issues and type (poor concentration/feeling detached/temporary loss of memory) Symptom spread including first/last symptom and speed
Patient medical, social and family history	Medical history (migraine/other headaches/hypertension/high cholesterol/atrial fibrillation/diabetes/angina/myocardial infarction/seizures) Current medication (aspirin/clopidogrel/dipyridamole/ticagrelor/warfarin/dabigatran/rivaroxaban/apixaban/edoxaban/other anticoagulant/statin/other cholesterol treatment/blood pressure medication/anxiety or depression medication) Cigarette/E-cigarette smoker Alcohol consumption Caffeine consumption Family history of headaches or migraine Employment status (working/homemaker/unemployed/in education/retired) Computer/screen use (typically every day/most days/sometimes/rarely/never) Driver For females: pre-menopausal/peri-menopausal/post-menopause/receiving hormone treatment
Specialist initiated investigations undertaken/requested	Blood pressure (systolic value/diastolic value) 12 lead ECG Brain imaging (CT/CTA/MRI/MRA/other) Carotid doppler Transthoracic echocardiogram Portable ECG telemetry (eg, Holter or patch) Other investigation
Specialist initiated treatment	Medication started or recommended (aspirin/clopidogrel/dipyridamole/ticagrelor/warfarin/dabigatran/rivaroxaban/apixaban/edoxaban/other anticoagulant/statin/other cholesterol treatment/blood pressure medication/headache or migraine medication) Endarterectomy referral DVLA advice given Headache service referral Neurology service referral Advice given about managing headaches or migraines Other treatment

CTA, computed tomography angiography; MRA, Magnetic Resonance Angiography; TIA, Transient ischaemic attack.

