#### Prognostic model and risk assessment tool development

Development of the risk assessment tool will combine information from both Study A and Study B. Using the stages described by Moons *et al*^25 26^ and applying Transparent Reporting of a Multivariable Prediction Model for Individual Prognosis or Diagnosis (TRIPOD) Statement principles,^27^ a prognostic model will be developed through multiple regression to examine the association between clinical characteristics recorded during initial specialist TIA review (including demographics, symptoms and previous medical history) and the 90 day occurrence of any stroke. The initial model will contain all baseline factors independently associated with day 90 stroke and those nominated as plausible by clinicians during Study B initial co-design rounds. Backward stepwise regression will retain variables for the final prognostic model. The performance of the model will be summarised using calibration and discrimination measures. To correct for overfitting and optimism in model performance, an internal validation using bootstrap samples will be performed which splits the data into training and test samples multiple times.

Approaches to visually represent the prognostic model (eg, nomogram)^28^ will be prepared and shared with clinicians during the final round of the study B co-design process to confirm clinical sense and meaning. These will include simple and more complex risk tool options and their matching predictive performance statistics. Options will include clinician preferences about risk assessment tool format identified during the earlier co-design rounds. The final tool preferred by clinicians is expected to reflect a balance between predictive performance and a format/content which is suitable for real world clinical use^29^ e.g. it can be completed within the time restrictions of clinical care with information that is often available, while retaining acceptable utility.

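### Participant-recalled predictors may be collected up to a week after the TIA review, so some can be recorded after an early stroke, although the model section says they come from the review itself

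*Protocol article*

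**What the plan says.** All references are to the protocol article.

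- **Baseline data collection** sets the window: "baseline data collection is performed within 1 week of the TIA review". It allows three routes. Two are contemporaneous: "The data may be collected directly from the patient during the TIA review, from the medical notes made by the clinician at the review". The third is later: "via an additional telephone/video-conferencing/in person discussion held with the participant at the earliest opportunity (and within 1 week of the review".
- **Prognostic model and risk assessment tool development** describes the candidate predictors as "clinical characteristics recorded during initial specialist TIA review (including demographics, symptoms and previous medical history", to be related to any stroke within 90 days. Backward stepwise selection and bootstrap internal validation follow.
- **Population** adds a further delay before the review: "Initial review conducted within 1 week of last symptoms".
- **Participant identification and consent** lets the study be introduced after the review by post, email or telephone, so later contact is a planned pathway.
- **Background** gives the timing of risk: "TIA is associated with a 5% risk of stroke after 7 days and 10% during the next 90 days".

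The article does not say that recalled items must be obtained before any outcome stroke, or how they are handled if they were not.

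**The concern.** The two sections cannot both describe the same predictor set. If the later discussion is a source, some predictors were not recorded during the review.

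The mismatch matters because the extra week lies inside the outcome period. Suppose a participant is reviewed on day 0, has a stroke on day 3 and is interviewed on day 5. The answers about the original symptoms are then given with the stroke known. Symptoms here are mostly subjective and unwitnessed, and the interview may come up to two weeks after them (one week to review plus one week to interview). Weakness or speech loss may be recalled more readily, or differently, by someone who has just had a stroke.

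A predictor measured this way can look prognostic when it is not, and stepwise selection may keep it. Each bootstrap sample is drawn from the same records and carries the same bias, so the optimism correction leaves it untouched. No external validation is planned that might expose it. The tool would be used with information available at the review, where this artefact is absent.

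**Working it through.** **1. The plan's own figures.** With 1% versus 0.015%, two-sided 5% and 90% power, the usual two-proportion formula gives 1092 per group. With the continuity correction it gives 1287 per group, 2574 in total, which matches the Sample size section. Expected events at those rates: 1287 × 0.01 + 1287 × 0.00015 = 12.87 + 0.19 = 13.06, about 13. In the 10% scenario, 1287 × 0.10 = 128.7, matching the stated 128.

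**2. Ceiling.** From Background: 5% / 10% = 50% of 90-day strokes fall in the first 7 days. That clock starts at the TIA. The collection week starts at the review, so 50% applies only if review coincides with the TIA.

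**3. Share in the week after review.** Let H be the cumulative hazard from the TIA, with H(7) = −ln 0.95 = 0.0513 and H(90) = −ln 0.90 = 0.1054. For a review s days after the TIA in someone still stroke-free:

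share = [1 − exp(−(H(s+7) − H(s)))] / [1 − exp(−(H(s+90) − H(s)))]

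Two assumed shapes pass through both points:
- Weibull: H(t) = H(7) × (t/7)^k, with k = ln(0.1054/0.0513) / ln(90/7) = 0.282.
- Piecewise constant: 0.0513/7 per day to day 7, then (0.1054 − 0.0513)/83 per day.

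| Review after TIA | Weibull | Piecewise constant |
|---|---|---|
| 0 days | 0.0500/0.1000 = 50% | 0.0500/0.1000 = 50% |
| 1 day | 0.0233/0.0732 = 32% | 0.0436/0.0940 = 46% |
| 3 days | 0.0162/0.0638 = 25% | 0.0308/0.0818 = 38% |
| 7 days | 0.0110/0.0548 = 20% | 0.0045/0.0569 = 8% |

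For delays of 1 to 7 days the range is 8% to 46%. Applied to 13.06 events: 0.08 × 13.06 = 1.0 and 0.46 × 13.06 = 6.0, so about 1 to 6 strokes in the collection week.

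**4. Effect on one predictor (illustration).** Assume a symptom truly present in 30% of everyone (odds ratio 1.0), reported by 60% of those interviewed after a stroke. Both percentages are assumptions. With m of 13 stroke cases interviewed afterwards:

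recorded prevalence = [(13 − m) × 0.30 + m × 0.60] / 13; reference odds = 0.30/0.70 = 0.429

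| m | Prevalence in strokes | Odds | Apparent odds ratio |
|---|---|---|---|
| 1 | 4.2/13 = 32% | 0.477 | 1.1 |
| 2 | 4.5/13 = 35% | 0.529 | 1.2 |
| 4 | 5.1/13 = 39% | 0.646 | 1.5 |

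The number m cannot exceed the strokes occurring in the collection week, and it will be smaller wherever the items were taken at the review or from its notes.

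**The case against.** Several points on the other side are sound.

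- **Most data should be contemporaneous.** Collection at the review and from its notes are both allowed, services are commonly one-stop, and any later discussion is to happen as early as possible. This reduces the number affected but does not stop a post-stroke interview.
- **Symptom items are anchored.** Table 1 ties them to the referring event and the latest episode preceding the review, so symptoms of the stroke itself do not belong in baseline. Recall of the earlier episode can still be coloured by what followed. Age and sex are little exposed.
- **The article is condensed.** Table 1 is a summary, and the case report form is not shown. That it lists no date or source for the symptom items is not itself an error. The point rests on the conflict between two stated rules.

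A reader might go further and infer that the more-likely-diagnosis label is also entered with hindsight, inflating the comparison between diagnosis groups. The documents do not support that. The label is an entry criterion: "Following initial review, a specialist clinician symptom-based diagnosis is either possible migraine or possible TIA with migrainous symptoms". Table 2 records later diagnosis changes separately, and a discussion with the participant cannot supply the specialist's view. Nor is this incorporation bias: the outcome panel is not given the site diagnosis or the entry diagnosis. Only the confidence rating lacks a separately stated time, and its role is exploratory.

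**Conclusion.** The point holds for participant-recalled symptoms and history. The stated collection rule permits these predictors to be recorded after the outcome, it conflicts with the model section, and the planned internal validation cannot detect the resulting bias.

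The size is uncertain. It depends on the hazard shape, on review delay, and on this cohort sharing the time pattern of typical TIA; the Sample size section says it is unknown whether its 90-day risk is that of typical TIA. Background mentions a target for patients to be "reviewed by a specialist hospital service within 24 hours of symptoms being reported", but delay in reporting adds to that, so the 1-day and 3-day rows are illustrations, not estimates. The size and direction of any recall difference are assumed.

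Two larger figures are tempting. One is that half of the strokes fall in the window, but that is a ceiling on the wrong clock. The other is an odds ratio of about 1.8, which needs 6 of 13 cases affected: (7 × 0.30 + 6 × 0.60)/13 = 44%. That requires the top of the range and every such patient interviewed only after the stroke. A modest distortion is more plausible, but with about 13 events at the planning rates a few affected records can matter.

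**What to change.** 1. Reconcile the two sections: state which predictors may come from the later discussion, or restrict the model to items documented at the review.
2. Record the date and source (at review, review notes, later discussion) of participant-recalled items, so that they can be set against any stroke date.
3. For anyone whose stroke preceded the later discussion, use only items documented at the review.
4. Repeat the model with review-documented items only, as a sensitivity analysis, and report the change in retained predictors, discrimination and calibration.
5. State that the confidence rating is the one given at the review.

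The cost is a few database fields, one data rule and one extra model run. Eligibility and sample size are unchanged. The downside is some missing symptom items in the few patients with very early stroke. At submission 586 of 2709 participants were enrolled (586/2709 = 22%), so most of the cohort can be covered prospectively. For those already enrolled, source and date can be completed from the notes where possible.
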